## Abstract

**Background:**

Rheumatic heart disease (RHD) is a leading cause of preventable cardiovascular morbidity and mortality among children and young adults in low- and lower-middle-income countries. Acute rheumatic fever (ARF), the immunologic precursor to RHD, is frequently missed in endemic settings, resulting in delayed treatment and progressive valvular disease. Nepal bears a high burden of RHD but lacks a coordinated system for early ARF identification, standardized echocardiographic evaluation, and longitudinal follow-up.

**Methods:**

This protocol describes implementation of a standardized ARF case-finding program and integrated clinical and echocardiographic registry across 11 district and referral hospitals in Nepal. The program is delivered through the PRIMA Network in partnership with the Kathmandu Institute of Child Health (KIOCH), embedded within existing PEN-Plus chronic disease infrastructure at district-level facilities. Case-finding is integrated into routine care using the 2015 modified Jones criteria, standardized echocardiography protocols, centralized training, and REDCap registry-based follow-up. Implementation outcomes are evaluated using Proctor's taxonomy, focusing on acceptability, feasibility, and adoption of the program within routine care, rather than on clinical detection rates or RHD outcomes. Contextual determinants are examined using the Consolidated Framework for Implementation Research (CFIR). Care-process indicators including diagnostic patterns and follow-up completion are summarized descriptively over the first 12 months of program delivery.

**Discussion:**

This protocol describes a pragmatic approach to embedding ARF case-finding within routine district-level care in Nepal. Findings will inform future evaluations of program performance, scale-up, and sustainability, and may serve as a replicable model for strengthening ARF detection in other RHD-endemic low-resource settings.

## Introduction

1

Rheumatic heart disease (RHD) remains one of the leading causes of preventable cardiovascular morbidity and mortality among children and young adults in low- and lower-middle-income countries (LMICs), including in the South Asia region (1). Untreated Group A streptococcal (GAS) pharyngitis leads to acute rheumatic fever (ARF), an immunologic response which eventually causes the cardiac valve damage characterizing RHD. Within South Asia, Nepal is recognized as an endemic country for RHD, reflecting ongoing transmission of GAS infections and persistent gaps in early detection and prevention.

Nepal is a mountainous country bordered by the Himalayas with the largest rural proportion in the region of South Asia (2). Rural households in hill and mountain districts often face difficult terrain, monsoon, landslides, and floods, that impede timely access to health facilities, particularly for non-emergency conditions such as sore throat. Prevalence of RHD in Nepal is high and increases with age, with an estimated 5.5 per 1,000 children 5 years of age with borderline or definite RHD and 16.0 per 1,000 in children 15 years of age (3) according to school echocardiographic screening studies. Regional variation within Nepal has been found, with higher prevalence of RHD in the Southern region compared to other regions (4). An estimated 20.1% of Nepal's population, approximately six million people, meet criteria for multidimensional poverty (5). The highest levels of poverty are in Southern Nepal, corresponding to the region with the highest RHD prevalence (4).

There have been important efforts by the Nepal Heart Foundation to establish a nationwide RHD registry (4), however most children in Nepal continue to be diagnosed late—after the development of clinically important heart disease. These gaps persist in part because of the low awareness of ARF among clinicians and the community, the lack of standardized echocardiographic assessment at the district level, and the absence of longitudinal clinical registries that track referrals between levels of the health system and follow-up. This program builds on the joint structure of decentralized rural care via PEN-Plus and ARF case-finding for biomarker discovery as part of PRIMA and is made possible by efforts from both Networks. Joint PEN-Plus and PRIMA efforts place an emphasis on ARF case-finding, early detection of ARF and RHD, improved access to care for this population, and high-quality follow-up in rural hospitals.

This implementation protocol, guided by the TIDieR (6) and StaRI (7) reporting frameworks, describes the implementation of an ARF case-finding program and integrated RHD clinical and echocardiographic registry in Nepal, with a focus on evaluating whether this program can be feasibly and acceptably embedded within routine health system care.

### Objectives

1.1

The primary objective of the study described in this protocol is to assess the acceptability, feasibility and facility-level adoption of the described ARF case-finding and registry program embedded within routine district and referral hospital care across diverse geographic settings in Nepal. This study does not evaluate the clinical effectiveness of ARF case-finding or its impact on RHD outcomes, which are beyond the scope of this early implementation evaluation.

Secondary objectives are: to measure fidelity to standard operating procedures (SOPs), defined as adherence to ARF diagnostic criteria, echocardiographic protocols, and registry documentation requirements; to describe the penetration of ARF case-finding within participating facility catchment areas; to evaluate short-term sustainability, defined as continued program operation and sustained workflow adherence at 12 months; to identify contextual factors associated with variation in adoption and fidelity across KIOCH and referral facilities using selected Consolidated Framework for Implementation Research (CFIR) domains.

## Methods and analysis

2

### Study design

2.1

This is a protocol for a prospective, pragmatic, multi-site implementation study conducted across six district and five referral hospitals in Nepal. This observational study evaluates early implementation of a standardized ARF case-finding and registry program embedded within routine inpatient and outpatient care. The primary unit of analysis is the participating facility, reflecting integration of the standardized workflow across Nepal's diverse geographic and socioeconomic health system contexts. Implementation outcomes will be evaluated over the first 12 months of program delivery after a two-month run-in period (April 2026-April 2027) using a mixed-methods, registry-based approach. The study is conducted within the broader PRIMA research platform but focuses specifically on implementation of the ARF case-finding and registry workflow.

Recruitment activities began in February 2026 and will continue on a rolling basis across participating facilities.

### Conceptual framework

2.2

This study is guided by an implementation science framework based on Proctor's taxonomy of implementation outcomes (8), which is described in Supplementary Table S1. At this early stage of program delivery, we are evaluating the acceptability, adoption, feasibility, fidelity, penetration, and short-term sustainability of a standardized ARF case-finding and registry program embedded within routine clinical care.

Within this framework, acceptability refers to user, provider and other stakeholders perceived perception of the appropriateness of the program, adoption refers to initiation of the standardized workflow across participating facilities, feasibility reflects the extent to which the workflow can be successfully carried out within existing clinical systems, fidelity captures adherence to diagnostic and registry SOPs, and short-term sustainability assesses continued operation at 12 months. Penetration and exploratory care-process indicators are examined to contextualize early implementation performance.

The conceptual model underlying the program is described in Figure 1. The model depicts contextual factors, program inputs, core intervention components, and implementation strategies leading to evaluation of adoption, feasibility, fidelity, and short-term maintenance. Long-term clinical effectiveness, including impact on ARF incidence or RHD progression, is beyond the scope of this initial implementation evaluation.

**Figure 1 F1:**
[figure not shown]
Conceptual model for the ARF case-finding and registry implementation study in Nepal. The model depicts how program inputs and implementation strategies are expected to produce measurable implementation outcomes, which are evaluated during the first 12 months of program delivery.

### Study setting and context

2.3

KIOCH is a not-for-profit organization established in 2017 to develop a hub-and-spoke network of multispecialty pediatric facilities in Nepal. KIOCH's mission is to provide timely, accessible, high-quality health care to all Nepali children irrespective of their economic status, with an initial focus on cardiology and cardiothoracic surgery, oncology, mental health, emergency, and critical care. This network, which is still in development, includes a central hub hospital in Budhanilkantha Municipality, Kathmandu, and satellite units in each province, with a strong emphasis on community outreach, school health programs, and district health system strengthening. The Preventing Rheumatic Injury biomarker Alliance (PRIMA) Network has partnered with KIOCH to leverage this emerging infrastructure for the implementation of their biomarker study across KIOCH facilities.

### Integrating ARF case-finding into Nepal's health system

2.4

PRIMA is a multi-country research network focused on improving early detection of ARF through harmonized clinical phenotyping and biomarker discovery. To support this goal, participating countries implement standardized ARF case identification, clinical characterization, registry infrastructure, and longitudinal follow-up protocols to ensure consistent phenotyping across recruiting facilities.

Many of the participating district-level hospitals in this study are implementing the WHO-endorsed Package of Essential Noncommunicable Disease Interventions–Plus (PEN-Plus) strategy (9), which decentralizes care for severe chronic noncommunicable disease to first-level referral hospitals in low-resource settings, primarily in Sub-Saharan Africa and South Asia (10, 11). The decentralization approach that PEN-Plus uses centers on task-sharing, standardized treatment protocols, and longitudinal follow-up for complex conditions (such as RHD) at district-level hospitals that are more geographically accessible to rural populations than tertiary care centers in urban areas (12), allowing ARF and RHD services to be embedded into routine care.

The 11 participating facilities are located across Nepal as pictured in Figure 2, and characteristics of each facility are listed. Together, the participating district and provincial hospitals serve an estimated combined catchment population of approximately 4–5 million people across urban, semi-urban, and rural regions of Nepal, or 1/6 of Nepal's total population.

**Figure 2 F2:**
[figure not shown]
Location of participating facilities in Nepal and characteristics of each facility.

### Study population

2.5

The target population includes children and adolescents aged 5–18 years presenting to participating facilities or found in community outreach with fever, joint pain, or other symptoms suggestive of ARF which would warrant full screening using the Jones criteria (13), as well as a history of sore throat. Children presenting at the listed facilities will be screened for ARF and RHD. Children diagnosed in schools or other community settings will be referred to the nearest participating facility for evaluation.

### Intervention description and procedures

2.6

#### Community case-finding procedures

2.6.1

To address poor health-seeking behavior and limited community awareness of ARF, a community-based case-finding approach will be implemented across participating districts. Female Community Health Volunteers (FCHVs), supported by trained healthcare workers, will conduct community-level awareness activities focusing on sore throat, early ARF symptoms (predominantly a combination of fever and joint pain), potential complications, and the importance of timely treatment. Following sensitization, FCHVs will undertake symptom-based screening and basic clinical assessments during routine community visits.

Referral to a participating facility is triggered by the presence of symptom combinations consistent with possible ARF, primarily fever with joint involvement, rather than any single symptom in isolation; a standardized symptom checklist was distributed to FCHVs and school personnel during training to guide this assessment.

In parallel, a school-based approach will complement community-level case detection. School nurses and teachers will be oriented on ARF symptom identification, early diagnosis and treatment, and referral pathways. Following sensitization, trained healthcare workers will conduct clinical screening, including cardiac auscultation and abbreviated echocardiography protocols using portable machines, in schools within participating districts.

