#### Clinical evaluation workflow

2.6.2

ARF cases will be diagnosed if children meet 2015 modified Jones criteria (13) for high-risk populations. Nurses and physicians at participating facilities will confirm the diagnosis through laboratory tests, physical examination, and echocardiography. ARF diagnostic criteria included in SOPs and REDCap registry forms guide providers in confirming diagnostic criteria for enrollment.

Cases that are determined to be likely ARF are entered into the registry and their echocardiograms are uploaded for review by cardiologists. There are several participating cardiologists at tertiary care facilities in the capital city of Kathmandu who will provide diagnostic support and clinical advice as requested by study clinicians. Recruitment and follow-up will occur continuously, with structured follow-up visits scheduled at 3, 6, and 12 months post-enrollment for each ARF patient. Children requiring penicillin prophylaxis will be reviewed clinically in accordance with national follow-up guidelines. Follow-up will occur at the closest participating facility to the child's residence.

At each participating site, implementation is led by a designated clinical team comprising a physician, staff nurse, and laboratory technician. This team is responsible for application of ARF diagnostic criteria, echocardiographic assessment, registry documentation, and coordination of follow-up care.

Training was held by KIOCH in November 2025 during which SOPs for recruitment, ARF diagnostic criteria, and echocardiography protocols were reviewed with all providers and distributed. All facilities are expected to adhere to centrally defined SOPs and any deviations or contextual constraints will be documented in detail and reviewed during monthly monitoring and quality assurance meetings with the central KIOCH team.

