#### ARF diagnostic criteria

2.6.3

The 2015 modified Jones criteria (13) for high-risk populations will be used. The diagnosis of ARF is made if two major or one major and two minor criteria are met along with the evidence of streptococcal infection. If ARF is thought to be a recurrent episode, three minor criteria can be used to make the diagnosis. Major criteria include presence of carditis, mono- or polyarthritis, polyarthralgia, chorea, erythema marginatum, and subcutaneous nodules. Minor criteria include monoarthralgia, fever ≥38.0 °C, elevated inflammatory markers: ESR ≥30 mm/h and/or CRP ≥3.0 mg/dL, or prolonged PR interval on ECG. Prolonged PR interval is counted as a minor criterion only if carditis is not being used as a major criterion. There must be evidence of preceding group A streptococcal infection which is required for all except isolated chorea or indolent carditis. Antistreptolysin O Titer (ASOT) testing is provided to all facilities by the PRIMA study and will be the most common GAS antibody test used, though anti-DNase B titer, positive throat culture for GAS, and positive rapid antigen detection testing for GAS can also be used.

Carditis may be clinical or subclinical. Subclinical carditis is defined by Doppler echocardiographic evidence of pathological mitral or aortic regurgitation and morphologic changes as detailed in the 2023 World Heart Federation guidelines for the echocardiographic diagnosis of RHD (14). Echocardiographic assessments are performed using standardized imaging checklists which specifically include the criteria for pathological regurgitation and morphologic change. Echocardiograms are all uploaded for central review by cardiologists to support diagnostic consistency and fidelity. Kathmandu-based cardiologists serve as the final interpretive authority for echocardiographic findings, consistent with specialist referral practice within Nepal's health system. All clinics are equipped with a cardiac ultrasound machine.

Cases in which diagnostic criteria are not clearly met are reviewed by a study cardiologist, and children may be classified as suspected or probable ARF when appropriate. Diagnostic classification may be updated over time as additional clinical, laboratory, or echocardiographic information becomes available during follow-up, which reflects real-world practice.

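### The community referral rule rules out any single symptom and states no exception for chorea, a major criterion that the protocol itself recognises in isolated form

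*Protocol article*

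**What the plan says.** Section 2.6.1 (Community case-finding procedures) makes referral from the community depend on symptom combinations that suggest ARF, "primarily fever with joint involvement, rather than any single symptom in isolation". The tool for applying this is described only briefly: "a standardized symptom checklist was distributed to FCHVs and school personnel during training to guide this assessment". No exception to the single-symptom exclusion is stated.

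Section 2.6.3 (ARF diagnostic criteria) says: "Major criteria include presence of carditis, mono- or polyarthritis, polyarthralgia, chorea, erythema marginatum, and subcutaneous nodules". For a first episode the threshold is "two major or one major and two minor criteria are met along with the evidence of streptococcal infection". The same section waives the streptococcal requirement for isolated chorea and for indolent carditis. Children who do not clearly meet the criteria are reviewed by a study cardiologist and may be classed as suspected or probable.

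Section 2.6.2 (Clinical evaluation workflow) places confirmation at the facility: "Nurses and physicians at participating facilities will confirm the diagnosis through laboratory tests, physical examination, and echocardiography".

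Section 2.5 (Study population) describes the target population as children with "fever, joint pain, or other symptoms suggestive of ARF which would warrant full screening using the Jones criteria", and includes those found in community outreach.

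**The concern.** A combination rule for lay screeners is sensible when the symptoms are common and non-specific, as fever and joint pain are. Chorea is different within this protocol. It is a major criterion, it can be seen without equipment, and it is the one visible sign that the diagnostic section expects to occur alone. A blanket exclusion of single symptoms filters out that presentation at the community step, before the child reaches the tests that would settle the question.

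Two things are at stake. The first is clinical: such a child may be evaluated, and given prophylaxis, later than necessary. The second concerns a secondary outcome. Table 1 frames penetration as whether children with suggestive symptoms are found and evaluated, and it counts suspected as well as confirmed cases. Children whom the community route does not refer may be missing from those counts.

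**Working it through.** No figure in the document bears on this point and none needs reproducing. The check is to follow one child through the sections as written.

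1. **The child.** Chorea is the only visible sign. Fever and joint signs are absent, since either would make a combination.

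2. **Community step (2.6.1).** The child has one symptom. The rule asks for a combination and expressly sets aside a single symptom. The word *primarily* in the rule says which combinations matter most; it does not soften the single-symptom exclusion. Result: no referral is triggered.

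3. **Diagnostic criteria (2.6.3).** The same child already has one major criterion. A first-episode diagnosis still needs a second major criterion or two minor ones. With no fever or joint signs, the candidates are:
   - carditis, including subclinical carditis on echocardiography (major);
   - raised ESR or CRP (minor);
   - a prolonged PR interval on ECG (minor), subject to the condition that "Prolonged PR interval is counted as a minor criterion only if carditis is not being used as a major criterion".

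   If chorea remains isolated, streptococcal evidence is waived.

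4. **Where those results come from (2.6.2).** Laboratory tests and echocardiography are assigned to the participating facility. ECG is not assigned by name, but the community section does not mention it either. Volunteers make basic clinical assessments and cannot obtain any of these results.

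5. **If the threshold is not reached.** The child can still be classed as suspected or probable, but only after evaluation.

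6. **Is this an acknowledged limitation?** The Discussion says that symptom-triggered case-finding will miss subclinical carditis in children without symptoms. Chorea is a clinical sign, so that statement does not cover this child.

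7. **Other routes.** Section 2.5 provides for screening of children who come to a facility directly. Section 2.6.1 also has trained health workers screen clinically in schools, with auscultation and a shortened echocardiogram; it mentions no ECG or blood test there. Direct attendance depends on families seeking care, and 2.6.1 gives weak care-seeking as a reason for having the community arm.

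Steps 2 and 3 together are the finding: the diagnostic section anticipates a presentation that the stated community trigger does not refer. Its size cannot be derived, because the document gives neither the share of ARF that presents as chorea alone nor the share of children expected to arrive by community referral.

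**The case against.** The strongest reply is that the working rule lies in the checklist and the SOPs, which an article need not reproduce, and that the checklist may list chorea. This stands in part. It means that the finding is about the rule as printed, and that nobody should assume the checklist is wrong. It does not remove the finding, because the article states a rule without exception; if the checklist has one, the printed sentence is inaccurate and needs the same correction.

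A second reply is that a lay trigger may properly be narrower than the diagnostic criteria or the target population. This stands. A reader might infer that 2.6.1 contradicts the symptom list joined by *or* in 2.5. The documents do not support that: 2.5 describes whom the programme is for across all entry routes, and 2.6.1 describes one route.

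A third reply is that the same reasoning applies to other single major signs, such as subcutaneous nodules or erythema marginatum. As logic this is fair. What distinguishes chorea in the text is that 2.6.3 itself names its isolated form and relaxes a requirement for it. That supports a narrow exception and gives no ground for abandoning the combination rule.

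Finally, the text says what triggers a referral; it does not bar anyone from care, and volunteers are supported by trained health workers. This also stands and limits the likely harm.

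**Conclusion.** The point holds as a minor one. As printed, the volunteer and school-personnel rule does not refer a child whose only visible sign is chorea, although the protocol treats chorea as a major criterion and recognises its isolated form. The possible effects are delayed evaluation and slightly lower penetration counts. Acceptability, feasibility and adoption are unaffected. The study is descriptive and sets no thresholds for success, so no formal conclusion depends on this.

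The verdict assumes that the printed rule is applied literally and that the checklist contains no chorea exception. The second assumption cannot be checked from the article.

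Two stronger readings should be resisted. A reader might infer that the rule turns away children who already meet the diagnosis. It does not: under the stated threshold chorea alone is not sufficient, and only the streptococcal requirement is waived. A reader might also try to size the gap by counting which combinations of facility results would reach the threshold. Such a count depends on what is assumed about streptococcal evidence once carditis is found. With that evidence assumed present, it comes out the same for any other single major sign. It counts patterns, not probabilities, so it does not measure how many children are affected.

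**What to change.** In 2.6.1, add one sentence: suspected chorea on its own triggers referral to a participating facility. Keep the combination rule for all other symptoms. Then confirm that the checklist held by volunteers and school personnel says the same, and reissue it only if it does not.

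The cost is one sentence, one check and possibly a reissue. The downside is a few more referrals, some of which will not be ARF. Because the exception covers a single distinctive sign, the loss of specificity should be small, although the document gives no data from which to estimate it.
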